### Recruitment and randomization

Advertisements in local community newspapers which direct potential participants to contact the research coordinators (one in each province) via email or a toll-free number will be used to recruit participants. As well, LTC facilities and the Alzheimer Societies of Brant, Haldimand Norfolk, Hamilton Halton, Manitoba, Saskatchewan, Alberta/North West Territories, and Calgary, will assist with recruiting potential participants.

Research assistants will contact potential participants in each province via telephone to explain the study, answer any questions, and obtain informed verbal consent to participate. A tracking sheet of the numbers of potential participants who are approached to participate in the study, as well as the number of eligible consenters and non-consenters will be kept in a secure shared drive separate from the data. Reasons for non-consent will be documented.

A unique study identifier will be assigned to each participant to maintain confidentiality. REDCap will be used to randomly assign (1:1 ratio) participants to either the intervention or control group. Participants will be blinded to assignment status, and will be told that they will be offered one of two ways of providing support. In order for blinding to occur, the control group will be an educational control group receiving educational information. Two versions of the consent forms will be used one for the intervention and another for the control group (both versions of the consent forms are in the supplementary file). The RAs will read to the participants the version of the informed consent that will describe the study and group allocation procedures specific to their assigned group. Following the first interview, the informed consent will be emailed to participants. Data collection will then proceed with gathering demographic data and the baseline survey measures. Immediately following the baseline interview, all participants will be sent a copy of the appropriate consent form by email. Un-blinding will occur upon the request of the participant.

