**Methods:**

This study is a single blinded pragmatic mixed methods randomized controlled trial. Approximately 280 family carers of older persons (65 years of age and older) with dementia residing in LTC will be recruited for this study. Data will be collected at three time points: baseline, 2 month, and 4 months. Based on the feasibility study, *we hypothesize that participants using MT4C-In Care will report significant increases in hope, general self-efficacy, social support and mental health quality of life, and significant decreases in grief and loneliness from baseline, as compared to an educational control group*. To determine differences between groups and over time, generalized estimating equations analysis will be used. Qualitative descriptive analysis will be used to further evaluate MT4C-In Care and if it supports carers through transitions.

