### Data collection

Data will be collected during audiotaped telephone interviews by trained, site-specific research assistants (data collectors) at three time periods: baseline, 2 months and 4 months. The qualitative interviews will be conducted at 2 months. Data collectors will obtain verbal consent to participate in the study prior to each telephone interview. Table 1 outlines the data collection for this study using the SPIRIT table format.

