### Data management plan

All data collectors (i.e., research assistants) will login to REDCap (a secure web application) to enter the participants’ responses using the participant’s unique study ID. The use of REDCap significantly reduces errors in data collection and the amount of missing data. REDCap will be accessed using university iPads, desktop computers or encrypted laptops dedicated to the study. The digitally recorded qualitative interviews will be labeled with each participant’s study ID and uploaded to the secure password protected SharePoint site. The transcriptionist will also have access to this site and will upload all transcripts to this site as well. The Research Coordinator and site PI’s will also have access to this site. There will be no sharing of individual data because of consent procedures.

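### Assignment precedes an arm-specific consent reading and the baseline interview, and no one eliciting the outcomes is said to be blinded

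*Protocol article*

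**What the plan says.** All of this is in the protocol article.

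- **Consent forms (Recruitment and randomization).** After describing 1:1 assignment in REDCap, the section states: "Two versions of the consent forms will be used one for the intervention and another for the control group". The RA reads to the carer "the version of the informed consent that will describe the study and group allocation procedures specific to their assigned group".
- **Baseline (same section).** It continues: "Data collection will then proceed with gathering demographic data and the baseline survey measures".
- **Earlier contact (same section).** The preceding paragraph has RAs telephone potential participants to "explain the study, answer any questions, and obtain informed verbal consent to participate".
- **Who collects data (Data collection).** "Data will be collected during audiotaped telephone interviews by trained, site-specific research assistants (data collectors)" do so at baseline, 2 and 4 months. The section adds: "Data collectors will obtain verbal consent to participate in the study prior to each telephone interview".
- **Role (Data management plan).** "All data collectors (i.e., research assistants) will login to REDCap", so the two job titles denote one role.
- **Blinding (Abstract, Methods).** "This study is a single blinded pragmatic mixed methods randomized controlled trial". Recruitment and randomization says that participants are blinded and names no one else.
- **2-month interview (MT4C-In Care checklist).** Intervention participants complete a checklist on their use of the site during that interview.
- **Model (Outcome analysis).** The GEE contains group, time with baseline as one of its three levels, and group x time. The interaction is the test of effect.

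**The concern.** An RA cannot read the form for the assigned arm without knowing the arm. Two things then depend on allocation that should not.

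The first is who enters the data set. A carer who hears the arm-specific form and declines has been assigned but has given no baseline data. Intention to treat cannot retain someone with no measurements. Non-consenters and their reasons are logged, but the article does not say by arm, so a difference in refusal could go unseen.

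The second is how the scores are obtained. Baseline MCS is a post-allocation measurement taken by an interviewer who knows the arm, and it is the reference level for the interaction. The follow-up scales are self-reports spoken to an RA who may also know the arm. Any arm-dependent difference in elicitation, at baseline or at follow-up, goes straight into the estimated effect on the primary outcome and cannot be removed after recruitment.

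**Working it through.** **Order of events.** Three steps are stated in sequence: assignment, reading of the assigned group's form, then demographic and baseline data. The earlier general verbal consent may come before assignment. On that reading too, the arm-specific form lies between assignment and baseline, so both late refusal and an arm-aware baseline remain possible.

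**Is the order needed?** The sections on the educational control group and on the intervention both send the arm's materials by e-mail immediately after the baseline interview. Nothing but the two consent versions requires the arm to be known sooner.

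**The plan's own figure.** The article gives no figure for bias. Its one related figure, 89% power, is not changed by this point. It reproduces as a two-sided comparison of 45% with 30%: the repeated-measures factor is (1 + 2 x 0.5)/3 = 0.667, the effective size is 140/0.667 = 210 per arm, and power is 0.891.

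**Illustration.** The article supplies 140 per arm and a within-person correlation of 0.5. The refusal and shift sizes below are assumptions.

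For one baseline-to-follow-up contrast in SD units with no true effect, the SE of the difference in change is sqrt(2(1 - 0.5)) x sqrt(2/140) = 0.1195. With a bias b in that contrast, the two-sided error is Φ(b/SE - 1.96) + Φ(-b/SE - 1.96).

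*Selective refusal.* If a fraction f of one arm declines after hearing its form, and decliners differ from the rest by D in mean MCS, the arms differ at entry by about f x D. For f from 0.05 to 0.20 and D from 0.3 to 0.5 SD, that is 0.05 x 0.3 = 0.015 to 0.20 x 0.5 = 0.10 SD. What reaches the interaction depends on persistence:

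| Entry difference at follow-up | b (SD) | Two-sided error |
|---|---|---|
| Persists fully | 0 | 5% |
| Halves | 0.0075 to 0.05 | 5.0% to 7.0% |
| Vanishes | 0.015 to 0.10 | 5.2% to 13.3% |

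*Arm-dependent elicitation.* A shift at baseline only, or at follow-up only, is not cancelled:

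| b (SD) | b/SE | Two-sided error |
|---|---|---|
| 0.05 | 0.42 | 7.0% |
| 0.10 | 0.84 | 13.3% |
| 0.20 | 1.67 | 38.7% |

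If time is categorical and both follow-up contrasts carry the same b, the joint two-degree-of-freedom test gives nearly the same: 6.8%, 12.7% and 39.1%.

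The direction is not fixed. A selection advantage that fades would count against the arm that had it.

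**The case against.** Several points on the other side stand, and they limit what may be inferred.

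- **Concealment.** A reader might infer that allocation concealment is lost altogether. REDCap assigns centrally, and nothing suggests that an RA can foresee the next assignment. The general verbal consent may also precede it. The supported concern is refusal after assignment.
- **Same person.** A reader might infer that one individual recruits a carer and makes every later call. The article identifies RAs and data collectors as one site-specific role, not person by person. It also provides no separate or blinded assessor.
- **Contradiction in the label.** Calling the trial single blinded is consistent with blinding participants only, so it is no error.
- **A definite inflated error rate.** A reader might take an entry imbalance and compare the arms at follow-up alone. For an imbalance of 0.083 SD (90% against 75% consent, extra consenters differing by 0.5 SD: 0.5 x 15/90) that gives about 10.7%. The article does not plan that test. Under group x time, a constant imbalance is absorbed by the group term. If it halves by follow-up, the error is about 6.4%.
- **Safeguards.** The SF-12v2 has fixed responses, carers may hold a copy of the questionnaires during the call, interviews are audiotaped, and data collectors are trained and meet every two weeks. Carers are meant to be blind, and baseline precedes any materials. These measures reduce elicitation bias. They do not remove the interviewer's knowledge of the arm.
- **Unseen forms.** How much the two forms disclose is in a supplement that is not shown, so whether they would drive differential refusal is unknown.

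**Conclusion.** The point holds as a flaw in the order of enrolment and in who elicits the outcomes. As the article is written, assignment comes before the arm-specific consent reading and before baseline, so arm-dependent refusal and an arm-aware baseline MCS are both possible. Nothing blinds the RAs who ask the follow-up scales, and the intervention-only checklist in the 2-month interview discloses the arm again.

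The size is not derivable from the article. Selection matters only so far as it does not persist: over the assumed range the error stays between 5% and about 13%, and at or below 7% if half the difference remains at follow-up. Arm-dependent elicitation is the larger risk, at about 7% to 39% for assumed shifts of 0.05 to 0.20 SD. These figures rest on 140 analysed per arm, correlation 0.5 and no true effect, and they show sensitivity only. The case for change rests on the bias being irreparable afterwards while the order can be changed without delaying either arm's materials.

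**What to change.** 1. Replace the two consent versions with one neutral form. The article already intends to tell carers only that they will be offered one of two kinds of support.
2. Complete consent, demographics and all baseline scales, and only then release the REDCap assignment. Send the arm's materials by e-mail after the baseline interview, as already planned.
3. At 2 months, ask all outcome scales before the checklist, the qualitative interview or any other question about the site.
4. Where feasible, have an existing RA who handled neither that carer's allocation nor the checklist make the follow-up outcome calls. Because the 2-month checklist discloses the arm, this applies to the 4-month call too.
5. State in the protocol who is and is not blinded.
6. For anyone already assigned under the current order, report refusals after assignment by arm.

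The cost is a consent amendment at the four ethics boards named under Study design, a change to the REDCap workflow, and some scheduling burden for follow-up calls. Steps 2 and 3 mainly reorder work already planned. Step 4 is the one that strains staffing, so it is limited to where it can be done.

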### Educational control group

The educational resource that will be emailed to the control group participants is an Alzheimer Society document called *Progression* [26] immediately following baseline interviews*.* This document was developed for use by people with dementia and their family and friend carers. It provides a summary overview of the stages of the disease, importance of person-centred care, prompts to access support, and a list of additional resources. It is available for free on the Alzheimer Society of Canada website. Following data collection, control group participants will also be granted access to MT4C-In Care.

### Intervention: my tools 4 care-in care

The intervention group will receive via email the educational resource provided to the control group and instructions on how to access to the MT4C-In Care site immediately following baseline interviews. MT4C-In Care access will occur for 2 months via an assigned web link and unique username and password. Participants will access the MT4C-In Care tool as frequently as desired, and will choose which content to engage with. They may choose not to access MT4C-In Care at any time. Some activities prompt the participants to enter information into the site, and this information will not be accessed by anyone, including the research team. The components of MT4C-In Care include a home page which introduces the toolkit and sections: a) “About Me” (contains guided evidence-based activities), b) “Common Changes to Expect”, c) “Frequently Asked Questions”, and d) Resources. More detailed information about My Tools 4 Care-In Care is published elsewhere [24].

### Measures

#### Carer demographic form

A demographic form will be used to collect data from carers such as age, gender, language, relationship to the person living with dementia. Carers will also provide information about the person living with dementia including their stage of disease, age, gender, and length of time in LTC. A similar demographic form was used in the pragmatic trial of MT4C [20].

#### Process measures

Several process measures will be used throughout the study. Research assistants will track all participants’ participation in the study, including recruitment rates, and reasons for study withdrawal and missing data. The other measures include the MT4C-In Care checklist and qualitative interviews.

#### MT4C-in care checklist

MT4C-In Care checklist will be used to collect data on access and use of MT4C-In Care. Data will be collected at 2 months following the start of the intervention. Participants in the intervention group will be asked to complete the MT4C-In Care self-report checklist during the interview. The questions include: 1) how often they use MT4C-In Care, b) the total time spent on MT4C-In Care and c) content accessed over the past 2 months. They will also be asked three dichotomous questions about whether MT4C-In Care improved their knowledge and skills, mental health, and well-being, from their perspective. As well data will be collected on the utilization of other caregiver support websites and support groups. There will be no prohibited interventions during this study. A copy of the checklist can be found in the supplementary files.

#### Qualitative interviews

At 2 months, a sub-sample of 40 participants who received the intervention will be interviewed over the phone using a semi-structured interview guide. The nature of the questions will focus on participants’ experiences when working on MT4C-In Care, if it helped them deal with their significant changes, and what did they liked best and least. The qualitative interview guide was developed for this study and is found in the article’s supplementary files. The purpose of the interview will be to understand their perceptions of MT4C-In Care in more depth.

Based on our previous study [27], the sample should contain approximately 15 participants from each of Alberta and Ontario and 5 participants from each of Saskatchewan and Manitoba, or enough to obtain rich findings. Interviews will last between 15 and 30 min and will be audiotaped. The research assistant will record field notes that reflect the tone of the interview, any difficulties faced (e.g., multiple interruptions or feeling rushed), and initial thoughts related to salient points raised.

#### Outcome measures

The **Mental Component Summary (MCS) score**, short form Health Survey (SF-12v2) [28], is the primary outcome because MT4C-In Care aims, ultimately, to support carers’ psychological well-being [29]. The higher the score on the MCS, the higher the mental health. The **SF-12v2** measures perceived function and well-being with 12 items using a variety of Likert scales. A majority of carers are older adults, and the SF-12v2 has been used with community-dwelling older adults. The tool’s eight domains (physical functioning, role-physical, bodily pain, general health, vitality, social functioning, roles, and emotional and mental health) can be combined to derive scores (maximum 100) for a physical component summary (PCS) and mental component summary (MCS). The SF-12v2 is used widely and in a variety of populations, and evidence supports its internal consistency, reliability, and construct validity [30, 31].

We selected as secondary outcomes those variables which are the hypothesized mechanisms by which MT4C-In Care affects mental health including hope, general self-efficacy, social support, grief and loneliness. Therefore, these are the proposed proximal outcomes targeted by MT4C-In Care. Measures of hope, self-efficacy, grief, loneliness, and social support are:
The **Herth Hope Index (HHI)**: 12 items measure three dimensions of hope (temporality and future, positive readiness and expectancy, and interconnectedness [32]). Each item is rated with a 4-point Likert scale. Scores range from 12 to 48 (higher scores indicate more hope). The measure has been found to be a reliable and valid measure with carers [33, 34].The **General Self-Efficacy Scale (GSES):** 10 items measure ability to handle adversity, each rated with a 4-point Likert scale [35]. Scores range from 10 to 40 (higher scores indicate more self-efficacy). Evidence supports the measure’s reliability and validity across populations [36].The **Non-Death Version Revised Grief Experience Inventory (NDRGEI):** 22 items measure grief of people who are not bereaved, each rated with a 6-point Likert scale [37]. The scale has just two items that are different from the version of the scale used with people that are bereaved. Four domains are measured, including existential concerns, depression, guilt and distress. Scores range from 22 to 132 (higher scores indicate more grief and loss). Evidence supports the scale’s reliability and validity [36].The **Three-Item Loneliness Scale:** 3 items measure perceptions of companionship, each rated with a 3-point Likert scale [38]. Scores range from 3 to 9 (higher scores indicate more loneliness). The measure is based on items from the revised University of California Los Angeles loneliness scale, but contains fewer items, takes less than 2 min to complete, and was selected for the current study to prevent respondent burden. It is validated for use with older adults. Evidence supports its reliability, and convergent and discriminant validity [39].The **Multidimensional Scale of Perceived Social Support (MSPSS):** 12 items measure social support, each rated with a 7-point Likert scale [39]. Three subscales can be calculated, for significant others, family, and friends. The total score is an average, calculated by summing all items (which could range from 12 to 84) and dividing by 12 (higher scores indicate more social support). The measure is used widely and across populations. Evidence supports its internal and test-retest reliability, validity, and three-factor structure [40, 41].

### Power and sample size

We aim to recruit a convenience sample of 280 participants, 140 in each of the intervention and control groups. Our design for the outcome analysis includes three repeated measurements to observe how the change in outcomes over time differs between the intervention and control group. This sample size achieves 89% power to detect a 15% difference in the mental health summary score between the two groups over time, when alpha level is 5%. This calculation assumed a Compound Symmetry covariance structure, a proportion of 30% in group 2, and correlation between observations on the same subject of 0.50.

### Data collection

Data will be collected during audiotaped telephone interviews by trained, site-specific research assistants (data collectors) at three time periods: baseline, 2 months and 4 months. The qualitative interviews will be conducted at 2 months. Data collectors will obtain verbal consent to participate in the study prior to each telephone interview. Table 1 outlines the data collection for this study using the SPIRIT table format.

**Table 1 Tab1:**
[figure not shown]
Schedule of Enrolment, Intervention (MT4C-In Care), and Assessments

*HHI (Herth Hope Index), GSES (General Self Efficacy Scale), SF12-v2 (Short Form 12-version 2), NDRGEI (Non-Death Revised Grief Experience Inventory), MSPSS (Multi-dimensional Scale of Perceived Social Support)

Using participants’ email addresses, a study brochure with the research coordinator’s contact information, and a copy of all study questionnaires (watermarked “for reference only”), will be sent to all participants after initial contact. Participants may use the “for reference only” questionnaires as a resource when data collectors are asking them for a verbal response to the questions during the telephone interviews. All contact with participants, including email communication, will be tracked by the data collectors on a data collection tracking sheet. Two weeks prior to each scheduled interview, a reminder will be sent to the participants to promote study retention. If the participant requests a change in the date and time of an interview, or misses a scheduled interview, the interview will be re-scheduled within approximately 1 week before or after the interview due date.

Data collectors will be trained before the study begins and will meet every 2 weeks during the study to discuss issues and challenges with data collection in order to maintain reliability and validity of data. As well data collectors will be reminded at each meeting to report any adverse events from the trial as soon as it occurs. A resource list has been developed to provide to distressed caregivers during the study by data collectors and they will encourage caregivers to contact their family physicians if needed.

Data will also be reviewed monthly by a working group comprised of the provincial PIs, data collectors and a statistician to identify any concerns and make any necessary changes. Interim analysis will occur every 6 months and presented at research team meetings for discussion. At that time discussion will occur if there is any reason to terminate the trial based on the analysis. Because the intervention is minimal risk to participants the research team will function as a Data Monitoring Committee.

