## Methods/design

### Study design

This pragmatic mixed methods randomized controlled trial is longitudinal, multi-site, and involves repeated measures. Participants are randomly assigned to an intervention or control group using REDCap, a secure, password-protected web application housed by the University of Alberta. The intervention group receives an educational resource and access to MT4C-In Care over a two-month period. The educational control group also receives the educational resource but will not be granted access to MT4C-In Care until the study period is over. Recruitment and data collection are planned between February 2020 and June 2021 in four provinces (Alberta, Saskatchewan, Manitoba and Ontario). Outcome data collection will occur at baseline, and 2 and 4 months from the start of the intervention. Process data collected at 2 and 4 months include qualitative data related to participant perceptions of MT4C-In Care and quantitative data related to frequency of use. Quantitative and qualitative data related to study processes (e.g., frequency and reasons for missing data) will be collected concurrently throughout the study. The qualitative data will help to explain the quantitative findings.

Reporting of this protocol followed the SPIRIT (Standard protocol items: recommendations for interventional trials) [25] guidelines for reporting protocols (SPIRIT checklist in supplementary files). This study received ethical approval from the University of Alberta Health Research Ethics Board (#Pro00090771), University of Saskatchewan Research Ethics Board (#1385), Education/Nursing Research Ethics Board at the University of Manitoba (E2019:127), and the Hamilton Integrated Research Ethics Board (#7659). If there are any changes in the protocol an amendment will be sent to the respective ethics boards for approval.

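### Six-monthly interim analyses go to the research team, which may discuss termination, with no stated purpose or stopping criterion and a sample size built on a single 5% test

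*Protocol article*

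**What the plan says.** In the protocol article, the Data collection section (text after Table 1) states: "Interim analysis will occur every 6 months and presented at research team meetings for discussion". It continues: "At that time discussion will occur if there is any reason to terminate the trial based on the analysis". Because the intervention is judged to carry minimal risk, "the research team will function as a Data Monitoring Committee". The section does not name the variables analysed at the interims, say whether the arms are compared, give a threshold, or say which reasons could end the trial.

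Study design gives the calendar: "Recruitment and data collection are planned between February 2020 and June 2021".

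Power and sample size plans "280 participants, 140 in each of the intervention and control groups" and claims: "This sample size achieves 89% power to detect a 15% difference in the mental health summary score". Alpha is 5%, and interim looks are not mentioned.

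Three other places bear on the point:
- **Blinding.** The abstract calls the trial single blind, and Recruitment and randomization names the participants as the blinded party. The research assistants read each participant the consent form for that participant's arm.
- **Outcome collection.** The primary outcome, the SF-12v2 mental component summary, is self-reported and collected by research assistants by telephone (Outcome measures, Data collection).
- **Open analysis choices.** Outcome analysis leaves the coding of time to a plot of group means and leaves the link function and any transformation to the observed scores. The missing-data method is also to be settled after the data have been analysed.

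**The concern.** The article commits to repeated analyses that can lead to termination, while the design calculation allows for one test. If a nominally significant interim difference could end the trial, the chance of a false positive finding would exceed the 5% on which the trial is sized.

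The second issue does not depend on any boundary. The people running the trial would receive the interim results and decide on them. If those results are comparative, investigators would know the trend while participants are still being recruited and interviewed about how they feel. They would know it, too, before choosing how time is coded, which link is used and how missing data are handled. The reason given for having no separate committee is low risk to participants. That is a safety argument and does not deal with early sight of outcome results.

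**Working it through.** **1. Reproduce the plan's own power.** Inputs from Power and sample size: 140 per arm, three measurements, correlation 0.50 with compound symmetry, "a proportion of 30% in group 2", a 15% difference, alpha 5%. Read as 45% against 30%, two-sided:

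- Effective n per arm = 140 / [(1 + 2 × 0.50)/3] = 140 / 0.667 = 210.
- Null standard error, pooled proportion 0.375: √(2 × 0.375 × 0.625 / 210) = 0.04725.
- Alternative standard error: √[(0.45 × 0.55 + 0.30 × 0.70)/210] = 0.04668.
- Power = Φ[(0.15 − 1.96 × 0.04725)/0.04668] = Φ(1.23) = 89.06%.

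This matches the stated 89%. A one-sided test would give 93.9%, which does not match. The design is therefore sized for a single two-sided 5% test.

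**2. Count the looks.** February 2020 to June 2021 is about 16 to 17 months. Interims every 6 months fall near months 6 and 12, and month 18 lies beyond the end. That makes two interims plus the final analysis, or three looks.

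**3. Overall error if every look is a two-sided 0.05 test of efficacy that would be acted on.** With information fractions t₁ < … < t_K = 1, under no effect Z_k = Σ_{j≤k} √(t_j − t_{j−1}) ε_j / √t_k, where the ε_j are independent standard normal. The overall error is P(|Z_k| > 1.96 for at least one k). Results from 2 million simulated trials per row:

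| Looks | Information fractions | Overall error |
|---|---|---|
| 1 | 1 | 5.0% |
| 2 | 1/2, 1 | 8.3% |
| 3 | 1/3, 2/3, 1 | 10.7% |
| 3 | 6/17, 12/17, 1 | 10.5% |
| 3 | 6/16, 12/16, 1 | 10.3% |
| 3 | 4/12, 10/12, 1 | 10.3% |
| 3 | 2/12, 8/12, 1 | 11.5% |
| 3 | 2/13, 8/13, 1 | 11.7% |
| 4 | 1/4, 1/2, 3/4, 1 | 12.6% |

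The documents give no information fractions, so these are assumptions. The rows with 16 and 17 use the calendar. The rows with 12 and 13 assume steady enrolment that ends 4 months before the close (16 − 4 and 17 − 4). They count only carers whose outcome is in: with a 4-month lag, 6 − 4 = 2 and 12 − 4 = 8 months of enrolment; with a 2-month lag, 4 and 10. A slower start (10% and 50% of the information at the interims) would give 12.3%.

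**4. Overall error if efficacy cannot stop the trial.** Let an interim stop the trial only when Z < −1.96, and allow a claim of benefit only at the final analysis. The false benefit rate is then 2.51%, against the nominal 2.5% in that tail. There is no inflation.

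**5. Overall error with control (three equally spaced looks).**

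- p < 0.001 at both interims and 0.05 at the end: simulations gave 5.04% and 5.06%, so about 5.05%.
- Pocock: nominal p of about 0.022 at each look.
- O'Brien-Fleming: nominal p of about 0.0005, 0.014 and 0.045.

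**6. Who would see the results.** No arithmetic applies. The interim goes to research team meetings, and that team is the monitoring committee. Its membership is not listed. Data collectors are named in a different body, the monthly working group with the provincial lead investigators and a statistician. Nothing separates the interim results from those who recruit or interview.

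**The case against.** The strongest reply is that the article never says the interims test efficacy. The neighbouring sentences deal with adverse events, distressed carers and minimal risk, so a review of safety or conduct is a fair reading. Boundaries and alpha allocation are often left to an analysis plan, which is not shown here. This stands against any flat statement that the error rate doubles. A reader might infer that; the documents support it only under the condition in step 3, and under step 4 there is no inflation.

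It does not dispose of the point. Adverse events already have their own prompt reporting route, and data concerns have a monthly review, so a separate six-monthly analysis that can end the trial may well be an outcome look. That is inference. But the article does fix who receives the results and who decides on them, and a boundary set elsewhere would not change that.

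Two further readings are tempting and fail:
- **Unblinding.** A reader might infer that the interims would unblind the staff who collect outcomes. Those staff are not blinded: they read the arm-specific consent form, and the intervention group completes a usage checklist during the interview. What they might newly learn is the trend.
- **Membership and powers.** A reader might infer that interviewers attend the interim meeting, see results by arm and can alter the study on that basis. The article says neither of the first two, and it gives the role of making changes to the monthly working group.

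It is also fair to object that pooling adverse events over arms would hide a safety imbalance. That stands, and the fix allows for it.

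**Conclusion.** The concern holds in a conditional form. The article states that six-monthly interim analyses go to the team running the trial, with termination open, and it sizes the trial for one two-sided 5% test. It gives no purpose or criterion for stopping.

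The effect on type I error ranges from none to roughly double. It is none if only harm or futility can stop the trial. It is about 10.3% to 11.7% for three looks if each compares the arms at nominal 0.05 and significance is acted on. The upper figures rest on the assumed information fractions and on two interims taking place.

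The exposure of investigators, and possibly of data collectors who already know the allocation, does not depend on the boundary. It does depend on the results being comparative, which the article neither states nor rules out. Its size cannot be calculated from the documents.

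**What to change.** Replace the interim wording in Data collection with one paragraph that states:

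- The six-monthly reviews cover recruitment, retention, missing data and adverse events. No between-group outcome analysis is done before database lock.
- If an efficacy look is kept, it uses the primary outcome with p < 0.001 at each interim and 0.05 at the final analysis. The choices on time, link function and missing data are then settled in writing before the first look.
- Any comparative results, including adverse-event counts by arm, are seen only by the trial statistician or others who neither recruit nor interview. The statistician does not bring them to the monthly working group. Adverse events stay visible by arm to that restricted group, so an imbalance can be noticed.

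The cost is a paragraph of protocol text and the team's early sight of arm-level outcomes. The sample size need not change: with p < 0.001 at the interims the final test stays at 0.05, and overall error is about 5.05%.
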